##### Additional aims

Models to track early developmental trajectories will be estimated in Mplus by latent class growth analysis with inter-individual variations in time of assessment and mixed-effect linear models with repeated measures to assess group differences in rates of temperament, emotional, and sensory profiles.

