### Measures

Demographic (e.g., parental age, parental job, and parental educational level), neonatal (e.g., gestational age, birth weight, and Apgar score), and clinical variables (e.g., NICU length of stay and minor morbidities) will be obtained from medical charts. Parent-report questionnaires are summarized and described in Table 2. As for behavioral coding purposes, the videotapes obtained from two cameras during the lab FFSF procedure will be edited offline using Movavi Video Suite 2020 software and a single synced video showing both frontal views of the caregiver and the infant’s face, hands, and torso will be produced. Videos will be micro-analytically coded for infants’ and caregivers’ target interactive behaviors according to an adaptation of the Parent–Infant Coding Scheme (PICS, Version 4.0; Brambilla et al., 2023) as reported in Table 2. PICS codes will be computed as a percentage of time for each FFSF episode (Table 3).

**Table 2 tab2:** Details of questionnaires included in the study.

Construct	Questionnaire	Reference	Item N	Likert scale	Description	Study wave(s)
Parental NICU-related stress	Parental Stressor Scale—NICU (PSS-NICU)	Miles et al. (1993)	46	5-point	Three main factor scores representing stress related to infants’ appearance, environmental sights and sounds, and parental role alteration	T1 (only VPT)
Sensory profile	Sensory Profile-2 (SP-2)	Dunn (2014)	54	5-point	The infant version (0–6 months) identifies 5 sensory patterns. The toddler version (7–35 months) identifies four sensory patterns.	T2, T3, T4
Anxiety symptoms	State–Trait Anxiety Inventory (STAI-Y)	Spielberger et al. (1983)	40	4-point	One trait score representing a tendency to feel anxiety and one state score representing the present levels of anxiety	T2, T4
Depression symptoms	Beck Depression Inventory (BDI-II)	Beck et al. (1996)	21	4-point	Global score representing a quantitative appreciation of the severity of symptoms of depression	T2, T4
Parenting stress	Parenting Stress Index—Short Form (PSI-SF)	Abidin et al. (2006)	36	5-point	Three subscale scores addressing parental distress, parent–child dysfunctional interaction, and stress related to difficult child behavior. A global score is also obtained.	T2, T3, T4
Temperament	Infant Behavior Questionnaire-Revised (IBQ-R) very short form	Gartstein and Rothbart (2003)	37	7-point	Three subscale factor scores addressing negative affectivity, surgency, and regulatory capacity.	T2, T3, T4

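### Latent class growth analysis allows no within-class variation, so at this trial's size ordinary stable differences between mothers or infants are likely to be reported as trajectory classes (exploratory analyses only)

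*Protocol article*

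**What the plan says.** Under Plan of statistical analyses, Additional aims, the protocol article names two methods in one sentence. The first is the class model: "Models to track early developmental trajectories will be estimated in Mplus by latent class growth analysis with inter-individual variations in time of assessment". The second is "mixed-effect linear models with repeated measures to assess group differences in rates of temperament, emotional, and sensory profiles".

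Table 2 (Measures) gives the waves for each questionnaire:

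- STAI-Y, two waves: "state score representing the present levels of anxiety T2, T4"
- BDI-II, two waves: "quantitative appreciation of the severity of symptoms of depression T2, T4"
- PSI-SF, three waves: "A global score is also obtained. T2, T3, T4"
- IBQ-R, three waves: "Three subscale factor scores addressing negative affectivity, surgency, and regulatory capacity. T2, T3, T4"
- SP-2, three waves but two forms: the infant version covers 0 to 6 months with five patterns, then "The toddler version (7–35 months) identifies four sensory patterns. T2, T3, T4"

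The article does not say which questionnaires enter the class model and which enter the mixed models. It gives no rule for choosing the number of classes. The section Additional exploratory aims presents this work as exploratory and as a guide to later studies.

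**The concern.** In LCGA the variances of the growth factors are fixed at zero within each class. Members of a class are assumed to differ from their common line only by errors that are independent between waves. The phrase about time of assessment concerns when people are measured; it adds no random intercept or slope.

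Temperament, parenting stress and anxiety are traits on which people usually differ stably. If the model cannot carry that stability inside a class, it carries it between classes. The number of classes then reflects how reproducible the score is and how it is distributed, not whether there are distinct developmental paths. Because these analyses are meant to steer later studies, artefactual classes could be taken forward as findings.

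**Working it through.** **Inputs from the article.** Under Statistical power and sample size estimates: 159 dyads (53 per arm) needed, 80 per arm (240) planned. From Table 2: two or three waves.

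**The plan's own figure.** For a one-way ANOVA with three groups, f = 0.25 and two-sided alpha 0.05, the noncentral F distribution with noncentrality N × f² gives power 0.7995 at N = 157, 0.8022 at 158 and 0.8049 at 159. The stated 159 in equal arms is reproduced. 53 × 1.5 = 79.5, hence 80 per arm and 240 in total.

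**Assumptions, not in the article.** Between-wave correlation rho, varied from 0 to 0.8; class number chosen by BIC; fixed assessment times.

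**Why extra classes are needed.** For person i in class k at time t, LCGA sets y = a_k + b_k·t + e, with e independent between waves. With one class the implied covariance between waves is zero. Any rho above zero contradicts the one-class model, even when no classes exist.

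**When BIC pays for a second class.** A second class adds three parameters (intercept, slope, class share). The penalty is 3·ln(N): 3 × 5.069 = 15.2 at N = 159 and 3 × 5.481 = 16.4 at N = 240. As a rough guide, the gain in twice the log-likelihood from representing the correlation in full is:

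- two waves: −N·ln(1 − rho²)
- three equally correlated waves: −N·ln[(1 − rho)²(1 + 2·rho)]

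At N = 159:

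- two waves: 159 × 0.0408 = 6.5 at rho 0.2; 159 × 0.0943 = 15.0 at 0.3; 159 × 0.1744 = 27.7 at 0.4
- three waves: 159 × 0.1098 = 17.5 at rho 0.2; 159 × 0.2433 = 38.7 at 0.3

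The gain passes 15.2 near rho 0.3 with two waves and already near 0.2 with three.

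**Simulation.** One homogeneous population with a continuous normal random intercept and no true classes; linear LCGA with residual variances by wave, equal across classes; one to four classes; 200 runs per cell. Share of runs in which BIC chose two or more classes:

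| rho | 2 waves, N=159 | 2 waves, N=240 | 3 waves, N=159 | 3 waves, N=240 |
|---|---|---|---|---|
| 0 | 0.5% | 0% | 0.5% | 0% |
| 0.2 | 14% | 18% | 69% | 87% |
| 0.3 | 56% | 78% | 99% | 100% |
| 0.4 | 94% | 99% | 100% | 100% |
| 0.5 or more | 100% | 100% | 100% | 100% |

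**Skewed scores** (exponential of 0.5 × normal). With two waves, two or more classes were chosen in 100% of runs even at rho = 0. With three waves and N = 159 the share was 91.5% at rho = 0 and 100% from rho = 0.2.

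**Does a one-class benchmark expose the problem?**

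- Normal scores: a one-class model with freely correlated waves had a lower BIC than every LCGA solution in at least 99.5% of two-wave runs at rho 0.4 or more, and in at least 94% of three-wave runs at rho 0.5 or more. At rho 0.3 with three waves and N = 159 it won in only 42.5%. In a smaller check at N = 159, the more economical one-class random-intercept model won in all 30 runs of each normal setting tried, including that one.
- Skewed scores: the freely correlated normal benchmark seldom won (three waves, N = 159: 0% at rho 0.5, 9% at 0.7, 38% at 0.8). Skewness has to be dealt with before the comparison means anything.

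**Is a normal growth mixture with a within-class random intercept a cure?** On homogeneous normal three-wave data it chose one class in 179 of 180 runs. On skewed three-wave data at N = 159 it chose one class in 0 of 60 runs at rho 0.5 and 0 of 60 at rho 0.6. It does not cure the problem for skewed scores.

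**Two waves, a separate limit.** Two points per person fix a straight line for each class, so trajectory shape cannot be assessed. There are also only three variance and covariance moments (two variances, one covariance), too few to separate intercept variance, slope variance, their covariance and residual variance.

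**The case against.** The best defence is that the analysis is exploratory, that the article already plans mixed models, and that rules for choosing and interpreting classes commonly sit in an analysis plan that is not shown. This stands as far as severity goes. It does not remove the point, because the article itself names LCGA, and zero within-class variance is part of that method. If the authors use the name loosely for a growth mixture model, they should say so.

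A reader might infer several stronger claims that the article does not support:

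- **False classes are certain.** They depend on the correlation, the score distribution and the selection rule, none of which is given. At low correlation with normal scores they are uncommon.
- **Too few waves cause them.** The direction is the reverse: at equal correlation, three waves give more false classes than two.
- **Two-wave classes come only from skewness.** A two-class linear model on two waves does have 7 parameters against 5 means, variances and covariances, but normal scores also produce classes through the correlation alone.
- **BDI-II and STAI-Y will be given class models.** The only link is the word for emotional profiles, which can equally belong to the mixed models.
- **Class membership will be compared between arms.** No such comparison is planned; group differences are assigned to the mixed models.

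**Conclusion.** The concern holds in conditional form. If BIC selects the classes, LCGA at 159 to 240 dyads is very likely to split a single homogeneous population once the between-wave correlation is about 0.4 or more (94% to 100% of runs), and for three-wave measures often at 0.2 (69% to 87%). Right-skewed scores make this worse. The cause is the absence of within-class variation. The straight-line limit for two-wave scales is a separate matter and applies only if those scales enter the class model. Severity is low: the analysis is exploratory, and neither Aims 1 and 2 nor the sample size is affected.

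**What to change.** - Make the mixed-effects model already planned the main trajectory analysis for all questionnaires, and the only one for BDI-II and STAI-Y.
- State which scales, if any, enter a class model. Limit these to measures with three waves on one common form, which in Table 2 leaves PSI-SF and IBQ-R. The SP-2 change of version after 6 months also affects a mixed model, so say how the two forms are linked or model only waves on the same form.
- Before interpreting classes, compare LCGA with a one-class random-effects growth model. Transform skewed scores first or use a non-normal within-class distribution; a normal random-intercept growth mixture is not a sufficient safeguard.
- Label any classes as descriptive.

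The cost is analysis-plan wording and some extra model fits, with no new data. The downside is that fewer classes, perhaps none, will be reported.

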## Discussion

The present protocol describes an RCT study that aims to assess the benefits of an early post-discharge video-feedback intervention to enhance and promote both parental and VPT infants’ outcomes. By collecting dual-source EEG data in a hyper-scanning paradigm and from face-to-face real-time interactions between parents and infants, the study also aims at providing estimations of the effects of such intervention not only for the individual adjustment of caregivers and infants but also for the emergence of dyadic co-regulatory biobehavioral processes. Such co-regulation profiles are meant to be critical indicators of a nurturing caregiving environment during the first months of life fostering affective wellbeing and stress resilience (Feldman, 2020; Levy and Feldman, 2019).

### Sources of bias and mitigation strategies

The heterogeneity of VPT infants’ conditions should not be underestimated. Even in the absence of severe comorbidities and brain injuries, the experience of NICU hospitalization might be very different for each infant and their parents. To avoid extreme variations, the gestational age range will be constrained between 28 and 35 weeks. Moreover, stress related to the NICU environment will be evaluated and quantified with a well-validated questionnaire (Miles et al., 1993). Selection issues might affect random allocation plans in RCT arms. The allocation to VPT-VF and VPT-CU arms will occur by using an automatically generated list of binary codes that will be consecutively matched with the enrolled families across consecutive sampling. This will reduce the risk of self-selection. To further avoid confounding by infant sex and assure sex distribution balancing, the random allocation will be stratified by infant sex by *post-hoc* controls every 20 enrollments. Parental gender will also be unconstrained, inviting the primary caregiver—and not explicitly the mother—to participate in the study, VF intervention, and observational procedures. EEG procedural steps and artifacts might easily result in the loss of subjects in a longitudinal study; a 50% oversampling was planned to achieve the minimum sample size for adequately powered statistical analyses.

### Expected results and impact

The project represents a translational application of the emerging field of hyper-scanning in developmental neuroscience (Provenzi et al., 2023). As neuroscience is moving toward a radical shift in considering interpersonal exchanges as the primary unit of analysis and observation (Leong et al., 2019; Hoehl and Markova, 2018), clinical applications are meant to be implemented to innovate healthcare. Previous proposals have been advanced to apply such a bi-personal neuroscientific approach to the field of adult psychiatry (Saul et al., 2022) and child development (Nguyen et al., 2020).

In this study, we aim to innovate the field of family-centered care in pediatric settings by embedding a cutting-edge approach to the study of parent–infant interaction and co-regulation processes into well-validated approaches to parental support and child development promotion. As the video-feedback intervention is well-acknowledged for its beneficial implications for parental wellbeing, child development, and quality of the early parent–child relationship (Fukkink et al., 2011; Montirosso et al., 2020), it represents an élite clinical setting to test the advantages of new neuroscientific-inspired metrics that specifically focus on the assessment of brain-to-brain co-regulatory processes. In this context, the present study has multifaceted implications.

From a scientific perspective, this study will provide first-of-a-kind quantitative estimations of inter-brain coupling and co-regulation in a sample of VPT infants and their caregivers. While previous research has highlighted functional and structural alterations in VPT infants’ brains (Dereymaeker et al., 2017; Hüppi et al., 1998; Pittet et al., 2019), very little is known about VPT neurophysiological functioning in real-life settings. Moreover, the study will provide insights into “how much” inter-brain synchrony should be expected in typical and atypical developmental trajectories. As medium levels of attunement and matching have been suggested to be optimal in terms of behavioral co-regulation during the first months (Provenzi et al., 2016), similar expectations appear to be plausible for what pertains to inter-brain coupling.

From a clinical point of view, the 2-BRAINED project is expected to produce evidence of the efficacy of an early intervention for VPT infants and their parents that is delivered after NICU discharge. This is a critical window for continuity of care as parents transition from potentially high-quality family-centered care during NICU stay to a lack of appropriate and tailored support at home (Lundqvist et al., 2019; Provenzi et al., 2016). From this perspective, this study will explore the efficacy of an intervention aimed at granting continuity of care from the hospital to the house, extending and empowering family-centered care for VPT infants’ parents.

From a translational neuroscience perspective, the study will also offer an unprecedented opportunity to obtain first-hand dyadic neurophysiological target outcomes of well-validated early family-centered VF intervention. While the road to developing qualitative and quantitative measures of the effectiveness and efficacy of such family-centered interventions is yet to be fully implemented, the integration of behavioral, self-report, and neurobiological markers is promising for future advances.

### Patient and public involvement

Active engagement of families will be pursued through public-dedicated web/social communications, digital content, and newsletters describing the achieved goals and implications of the study. Parental associations and professional orders will be engaged through online webinars to capitalize on the data obtained from the present study to further fuel a culture of family-centered care for preterm infants and their parents.

## Ethics and dissemination

### Ethics, privacy, and data management

The Ethics Committee Pavia and collaborating partners granted approval for the study on 16 February 2023 (protocol number: 0008588/23) and officially launched on 24 April 2023 (GR-2021-12375213). All procedures align with the ethical principles outlined in the Declaration of Helsinki for research involving human subjects, ensuring no harm to participants. The study intervention offers additional opportunities for families without altering standard mother–infant care programs. Infants will undergo planned diagnostic and therapeutic interventions at the child neurology and psychiatric unit IRCCS Mondino Foundation, Pavia, Italy, and the Scientific Institute IRCCS *E. Medea*, Bosisio Parini, Italy.

Data management will occur in accordance with the General Data Protection Regulation (Regulation 2016/279, commonly known as GDPR), to guarantee the privacy and the security of the gathered data. In this sense, all the infants’ parents will sign an informed consent module after that the study’s aims and modalities will be clearly explained and eventual doubts will be solved. Each subject will be assigned a code, and data will be stored in a pseudonymized form. After the period of conservation (25 years), data will be made completely anonymous. In line with the open science principle, the anonymized data collected for the study will be published on a publicly accessible “repository” (i.e., Zenodo) to promote the dissemination of research results with a view to furthering the research itself and the scientific community.

### Dissemination

The dissemination strategy involves presenting findings at national and international scientific meetings, publishing in developmental psychology journals, and engaging in outreach activities with families and healthcare specialists. This aims to promote early family-centered intervention and share insights with the wider public.
